### Modelling strategy

Our approach to model choice is based on four main criteria: the characteristics of the data, model pre-specification informed by the previous literature, diagnostic plots and assessment of model appropriateness. We will undertake exploratory analyses of the following possible interactions to assess whether the effect of the *Partnering with Parents* practice support system intervention is modified by factors such as the experience of carers, or number of children under the educators’ care. These analyses will inform the choice of moderators for the analysis described below. An a priori model-fitting analysis strategy will also be developed to identify the order in which covariates and moderator effects are to be included in the model. We will treat services and individuals as random effects to account for the correlation of outcomes for individuals that belong to the same cluster (within cluster correlation) [25], and repeated measures of the same individual over time (within-individual correlation).

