### Aims

This trial aims to evaluate the effectiveness of the *Partnering with Parents* practice support system by examining the following process information and intervention outcomes:
To what extent do educators, including educational leaders and practice coaches, use components of the practice support system? That is, which components are used, by whom, and how often? (Practice coaches are experienced educators in every service selected to assist other staff with implementation – see ‘Participants’, below)To what extent do educators, including educational leaders and practice coaches, find components of the practice support system useful?Following intervention, and compared with wait-list participants, to what extent are changes seen in educators’ reports of: quality of parent-educator relationships, skills and confidence in communicating with parents, and referral activities?Following intervention, and compared with wait-list participants, to what extent are changes seen in parents’: measures of quality of parent-educator relationships, satisfaction with communication at the service, perceptions of the relational environment at the service, help-seeking after advice from educators at the service, and parenting confidence and parenting stress?What process or demographic factors mediate or moderate the results obtained?To what extent do parents’ and educators’ responses correlate for common measures?

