### Analysis of primary and secondary outcome measures

An intention-to-treat multi-level analysis will be conducted for each of the outcome measures with level 1 data reflecting each assessment period, level 2 data reflecting individual participants and level 3 data reflecting the various services. Changes in the outcome measures will be compared for the intervention and control groups assuming appropriate distributions for the outcome measures. Random intercepts will be assumed, while allowing for the clustered nature of the data, and adjusting for appropriate covariates as fixed effects. The model will include an indicator variable for the study groups (0 = control, 1 = intervention) as a fixed effect at level 3 and an integer time variable (1 = baseline, 2 = time2 and 3 = time3) as a random effect at level 1.

We will report the estimated intervention effect as mean outcome difference for continuous outcomes and odds ratio for binary outcomes between intervention and control groups with 95% confidence intervals and *p*-values [25]. The effect of individual moderators will be incorporated using interaction terms between time, allocated group and the individual moderators [26].

Finally, a completer analysis will be conducted with a repeated measures MANOVA analysis using inverse probability weights to adjust for any attrition bias [27]. This analysis will also account for the correlation between measures from the same participant, while allowing for the clustered trial design.

Furthermore, we will examine responses of the control group before and after receiving the intervention.

As an indication of family-centredness, we will look at items that both educators and parents completed, to compare their perceptions (e.g. whether they both agree the service is a welcoming environment for parents).

All qualitative data (open text questions) will be summarised and examined for themes. Thematic analysis is a multi-stage process involving familiarisation with the data, coding (identifying important features relevant to the research questions), searching for and reviewing themes, and defining and naming them [28].

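### Moderators are chosen by exploring effect modification in the trial data and then estimated on the same data, so their nominal p-values and intervals are not valid

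*Protocol article*

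**What the plan says.** The Modelling strategy section of the protocol article opens with four criteria for model choice: "the characteristics of the data, model pre-specification informed by the previous literature, diagnostic plots and assessment of model appropriateness". It continues: "We will undertake exploratory analyses of the following possible interactions to assess whether the effect of the" practice support system is "modified by factors such as the experience of carers, or number of children under the educators’ care". The next sentence states what these analyses are for: "These analyses will inform the choice of moderators for the analysis described below". The section then promises a further step: "An a priori model-fitting analysis strategy will also be developed to identify the order in which covariates and moderator effects are to be included".

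Under Analysis of primary and secondary outcome measures, the article describes the three-level model and the reporting of the intervention effect, and then says: "The effect of individual moderators will be incorporated using interaction terms between time, allocated group and the individual moderators".

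Moderation is a research question in its own right. The Aims section asks: "What process or demographic factors mediate or moderate the results obtained".

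**The concern.** Read together, the two sections set out a two-step rule: look for factors that modify the intervention effect, then put the chosen ones into the outcome analysis. If both steps use the same outcomes, the second is not an independent look. A factor that seemed to modify the effect by chance in the first step will tend to do so again in the second, because the data have not changed.

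What is at stake is the answer to the moderation question in the Aims. A moderator reported at the end of this process would carry an ordinary p-value and 95% interval that ignore how it was chosen. Its estimate would tend to be too large, and a reader could not tell how many other candidates were examined and dropped.

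**Working it through.** **Do the two steps share data?** Whether an intervention effect is modified can be seen only in outcomes compared between arms. The Time 1 questionnaire precedes randomisation, so baseline data cannot show it. The 2018 field test is described in the Background without a control group. No other source is named. The planned blinding of analysts does not separate the steps either, since an interaction can be screened with coded arms.

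**Does other text fix the choice in advance?** The a priori strategy is "to identify the order in which covariates and moderator effects are to be included in the model". That sets the sequence of entry, not which moderators are eligible. Pre-specification from the literature is one of four criteria, alongside the characteristics of the data. The two named factors are examples in an open list.

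**How large is the false-positive risk?** The article gives no figure for the moderator analyses, so there is none to reproduce. Inputs:
- Level of 5%, two-sided, stated under Baseline analysis; its use for screening moderators is an assumption.
- Number of candidates k: two are named and the total is not given; 2 to 10 is assumed.
- Candidates independent and none a true moderator (assumption).

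The chance of at least one false moderator for one outcome is 1 − 0.95^k:
- k = 2: 1 − 0.9025 = 9.75%
- k = 4: 1 − 0.8145 = 18.5%
- k = 5: 1 − 0.7738 = 22.6%
- k = 6: 1 − 0.7351 = 26.5%
- k = 10: 1 − 0.5987 = 40.1%

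**Does the second step confirm anything?** A simulation used 118 educators in 19 services, a change score, an assumed intra-cluster correlation of 0.03, no true arm or moderator effect, and 4,000 runs per setting. Each candidate was screened at p < 0.05, and those that passed were refitted together on the same data. For the arm coefficient, moderators were given a mean of 1.5 standard deviations above zero (assumption).

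| k | At least one false moderator | Selected moderators significant again | Type I error of arm coefficient, uncentred | Same, centred |
|---|---|---|---|---|
| 2 | 9.0% | 97.1% | 8.3% | 4.6% |
| 4 | 17.4% | 93.5% | 12.3% | 4.6% |
| 6 | 26.4% | 94.5% | 15.7% | 5.0% |

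The second column agrees with the formula. The third shows that the retest is close to a repeat of the screen. With a looser screen at p < 0.10, only about half of the selected moderators are significant again (49% for k = 2, 47% for k = 6), yet the chance of at least one false moderator hardly moves (9.4% and 24.6%). Taking simply the strongest candidate gives 9.7%, 19.0% and 26.4% for k = 2, 4 and 6.

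**Why is the estimate exaggerated?** Under a 5% screen, a moderator is kept only if its estimate lies at least 1.96 standard errors from zero. If the true interaction is zero, every estimate that survives is therefore at least that far from the truth.

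**Is the intervention effect involved?** In a model with a group by time by moderator term, the group by time coefficient is the effect at moderator value zero. The last two columns show that this matters if moderators are uncentred and the reported effect is read from that model. With centred moderators the error rate stays at about 5%.

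**The case against.** Several points on the other side stand.

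- **The percentages measure multiplicity, not selection.** 1 − 0.95^k is what unadjusted testing of all k candidates would give with no screening step. The harm that selection adds is different: apparent confirmation, exaggerated estimates, and candidates that may go unreported.
- **The number of candidates and the screening rule are assumed.** The article says only that the exploration informs the choice. It states no threshold, and it names two factors.
- **Some of the detail belongs to an analysis plan.** Centring, the form of multiplicity adjustment and the exact list may be set out there, and their absence from an article is no fault. The objection here is to a stated rule, which such detail would not undo while the sentence stands.
- **The first step is already called exploratory.** That is so, but the label is not carried over to the moderator terms in the outcome analysis.

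A reader might also infer that the primary intervention effect is compromised. The documents do not support this. The outcome section states how the intervention effect will be reported before it mentions moderators, so taking the effect from a model without them is at least as natural a reading. The phrase about including moderators in the model points the other way but does not settle it.

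Nor does the text show that the problem recurs for every primary and secondary outcome. Experience and number of children in care are collected in the educator demographics and not in the parent demographics, and no link between individual parent and educator records is described.

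**Conclusion.** The concern holds for the moderator analysis. The article lets effect modification seen in the trial data choose the moderators that are then estimated on those data, so a reported moderator has no valid nominal p-value or interval and its estimate tends to be too large. Neither the a priori order of entry nor the reference to pre-specification cures this.

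The size is conditional. With independent candidates screened at 5%, the false-moderator chance per outcome is about 10% for the two named factors and 23% for five; 40% would require ten candidates, which nothing in the article indicates. A claim that every selected null moderator turns significant again would also go too far: the share was 93.5% to 97.1% under a 5% screen with two to six candidates, and about half under a 10% screen.

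The intervention effect is affected only if it is taken from the model with the interaction terms, and the inflation shown above requires uncentred moderators as well. The text leaves the source model open, so this is a point to settle and not an established error.

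**What to change.** - Delete the sentence "These analyses will inform the choice of moderators for the analysis described below".
- Close the list of moderators before outcome data by arm, coded or not, are examined.
- Report every listed moderator whatever its significance, either adjusted for multiplicity or labelled exploratory. Testing k listed moderators at 0.05/k, for example, keeps the chance of any false moderator at or below 5% per outcome.
- Label any moderator chosen from the data as post hoc.
- State that the reported intervention effect comes from a model without moderator interactions.

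The cost is wording only. According to Trial status and Data Availability, Time 2 data were still being collated, follow-up had not been collected and no dataset had been analysed, so at that stage the list could still be closed in time. The downside is that an unexpected moderator can be shown only as a post hoc finding.

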### Analysis of primary and secondary outcome measures

An intention-to-treat multi-level analysis will be conducted for each of the outcome measures with level 1 data reflecting each assessment period, level 2 data reflecting individual participants and level 3 data reflecting the various services. Changes in the outcome measures will be compared for the intervention and control groups assuming appropriate distributions for the outcome measures. Random intercepts will be assumed, while allowing for the clustered nature of the data, and adjusting for appropriate covariates as fixed effects. The model will include an indicator variable for the study groups (0 = control, 1 = intervention) as a fixed effect at level 3 and an integer time variable (1 = baseline, 2 = time2 and 3 = time3) as a random effect at level 1.

We will report the estimated intervention effect as mean outcome difference for continuous outcomes and odds ratio for binary outcomes between intervention and control groups with 95% confidence intervals and *p*-values [25]. The effect of individual moderators will be incorporated using interaction terms between time, allocated group and the individual moderators [26].

Finally, a completer analysis will be conducted with a repeated measures MANOVA analysis using inverse probability weights to adjust for any attrition bias [27]. This analysis will also account for the correlation between measures from the same participant, while allowing for the clustered trial design.

Furthermore, we will examine responses of the control group before and after receiving the intervention.

As an indication of family-centredness, we will look at items that both educators and parents completed, to compare their perceptions (e.g. whether they both agree the service is a welcoming environment for parents).

All qualitative data (open text questions) will be summarised and examined for themes. Thematic analysis is a multi-stage process involving familiarisation with the data, coding (identifying important features relevant to the research questions), searching for and reviewing themes, and defining and naming them [28].

The approach will be inductive – that is, coding and theme development directed by existing concepts or ideas. Thematic analysis will be undertaken by a researcher who has not been involved in collecting the qualitative information. To ensure generated themes accurately and consistently reflect all responses, a second researcher will independently recode responses based on themes outlined by the first researcher.

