## Methods

### Trial design

The trial is a cluster randomised controlled trial (cRCT) with two groups, an intervention and a wait-list control group. Because the intervention will be delivered under normal service conditions, a cRCT was chosen for practical reasons and to avoid contamination of individual participant randomisation. Each service participating in the trial is a ‘cluster’ and we used stratified randomisation to match each service with another. Following this we randomly allocated one of every pair to the intervention group and the other to the wait-list control group. Details of the randomisation procedure can be found in the ‘Randomisation’ section below. The wait-list control group receive *Partnering with Parents* after the intervention (see Fig. 1 for trial flowchart). The trial was designed and will be reported in accordance with the adaptation of the Consolidated Standards of Reporting Trials (CONSORT) reporting guidelines for cluster randomised trials [17].

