### Setting

ECEC has two broad service types: child care and pre-school services. In Victoria, Australia, according to the Australian Children’s Education & Care Quality Authority (ACECQA), there are 4241 ECEC services and just over 50% have an integrated kindergarten (pre-school) program with long day care. Local government or private providers operate the services with national or state funding. For this trial, we sought to recruit long day care, long day care with kindergarten, and stand-alone kindergarten ACECQA-approved ECEC services in Victoria. Using the contact details publicly available via ACECQA, two emails were sent (one in early December and one in late January) to 2589 Victorian services asking if they were interested in receiving more information about the experimental trial. We telephoned 41 sites that expressed interest and gave them information about the time commitment for implementing the intervention. During the phone call, three withdrew because of the time commitment and the remainders were sent a two-page information sheet and readiness checklist. After return of the readiness checklists, 28 services were sent a formal agreement to ‘sign up’ to trialling the intervention. Of these, 19 services returned signed agreements.

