### Randomisation

At the end of the Time 1 questionnaire collection period, services (clusters) were randomised to the intervention or wait-list control group. Services varied in size (i.e., number of families and staff), location, and their National Quality Standard (NQS) status and it is possible these characteristics could have an impact on outcomes (e.g., some larger services might have more resources than others). To control for possible influence of these characteristics, we used a stratified randomisation procedure to increase the similarity of the intervention and control groups. Stratified randomisation was a two-stage procedure [18]:

First, the project team matched every service with another by examining the following factors: location of service, size of service (number of staff and number of families), and their NQS status (their overall rating and their Quality Area 6 rating). This resulted in eight matched pairs as well as three small rural services grouped into one cluster, without a match. We decided to include the rural cluster in the study because their responses would still be valuable for analyses. For the purposes of randomisation for this rural cluster a ‘dummy site’ was used as their match, as the ninth pair, so that the services in the rural cluster were randomised to the intervention or wait-list control group the same way as all other services. To begin the second stage of randomisation we used the online software random.org [19] to create a random number order. An independent researcher at the PRC, who was unaware of the names or locations of services, performed the random number generation and assignment of pairs. Before the researcher began the randomisation procedure, we allocated each service an alphabetical letter. A random order of numbers from one to nine was generated, then, moving down the matched pairs list, the first random number was allocated to the first member of the first pair. This continued until the first member of every pair had a random number. Services with numbers one to five were allocated to the intervention group. Their pair was allocated to the control group. Services with numbers six to nine were allocated to the control group. Their pair was allocated to the intervention group. This process ensured each service had a 50% chance of being allocated to the intervention group.

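### The stated model does not follow the randomisation: 17 units in nine sets were allocated, but 19 unpaired services form the top level

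*Protocol article*

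**What the plan says.** Under Setting, "Of these, 19 services returned signed agreements". Trial design treats every one of them as a cluster ("Each service participating in the trial is a" cluster) and describes allocation within pairs: "we randomly allocated one of every pair to the intervention group and the other to the wait-list control group".

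Randomisation describes a different structure. Services were matched on location, size and National Quality Standard (NQS) status. "This resulted in eight matched pairs as well as three small rural services grouped into one cluster, without a match". For that rural group a dummy site "was used as their match, as the ninth pair". One random ordering of the numbers one to nine then settled all nine sets: "Services with numbers one to five were allocated to the intervention group", with their partners going to control, and the reverse for numbers six to nine. The three rural services are therefore all in the same arm. The article does not say which arm.

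Modelling strategy says "We will treat services and individuals as random effects". The section on primary and secondary outcomes sets a three-level model, with "level 2 data reflecting individual participants and level 3 data reflecting the various services", a group indicator at level 3, and covariates that are not named. Neither section mentions the pairs, the nine sets or the rural group.

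**The concern.** The standard error of a cluster trial should reflect the units that were allocated independently. Here the top level of the model differs from those units in two ways.

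- **Rural trio.** Three services share one allocation. Treating them as three independently randomised clusters claims information that the randomisation did not supply. If they resemble one another, intervals come out too narrow.
- **Matched pairs.** Sixteen services were allocated within pairs chosen to be alike. If the matching worked, leaving the pairs out keeps between-pair variation in the error term, and intervals come out too wide.

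The article promises, under Baseline analysis, to account for clustering so that intervals and type I error are correct. The stated model does not fully deliver that for this allocation. The article also uses the word cluster in two senses: each service is one under Trial design, while three services together are one under Randomisation.

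**Working it through.** **1. Count the units.** Services: 8 × 2 + 3 = 19, which agrees with Setting. Randomised units: 8 × 2 + 1 = 17 (the dummy is not a unit). Arms: 8 + 3 = 11 services against 8.

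**2. Degrees of freedom and two-sided 5% critical values.**

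| Analysis | df | t |
|---|---|---|
| 19 unpaired services | 19 − 2 = 17 | 2.110 |
| 17 unpaired units | 17 − 2 = 15 | 2.131 |
| 8 pairs, within-pair only | 8 − 1 = 7 | 2.365 |

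**3. The article's own sample-size statement.** It requires an effective sample of 102 and allows attrition below 50% (ICC 3%) or 33% (ICC 6%). Taking 102 as given, limit = 1 − 102 × [1 + (302/K − 1) × ICC] / 302, where K is the number of clusters.

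| K | ICC 3% | ICC 6% |
|---|---|---|
| 19 | 51.1% | 36.0% |
| 17 | 49.2% | 32.3% |

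Both rows lie near the stated limits. The unit count hardly moves the power statement, so the point concerns inference and not sample size.

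**4. Trio counted as three clusters.** Assumptions: 16 parents per service (302/19 = 15.9), total variance 1, a comparison of group means at one time, the trio sharing their whole cluster effect, and no pair effect. At ICC 6%:

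- Variance of a service mean: 0.06 + 0.94/16 = 0.1188.
- Variance of the arm difference if all services were independent: 0.1188 × (1/11 + 1/8) = 0.0256.
- Extra from the trio's three shared covariances: 2 × 3 × 0.06/11² = 0.0030, so the true variance is 0.0286.
- Expected residual variance: 0.1188 − (6 × 0.06/11)/17 = 0.1168, so the variance the analysis reports averages 0.1168 × 0.2159 = 0.0252.
- True SE over reported SE: √(0.0286/0.0252) = 1.065.
- Rejection rate: P(|t₁₇| > 2.110/1.065) ≈ 6.4%.

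The same steps give about 5.9% at ICC 3% and 6.8% at ICC 10%. Simulation of the nine-set allocation (40,000 runs each) gives 5.9%, 6.4% and 6.6% at ICC 3, 6 and 10%. With the trio averaged into one of 17 units and t on 15 df, it gives 4.9 to 5.0%.

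**5. Pairs left out.** The same simulation, now with half of the between-service variance shared within pairs (an assumption), gives these type I error rates at ICC 3, 6 and 10%.

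| Analysis | 3% | 6% | 10% |
|---|---|---|---|
| 19 services, t on 17 df, trio fully shared | 4.4% | 4.1% | 3.7% |
| 19 services, t on 17 df, trio sharing nothing | 3.6% | 3.0% | 2.4% |
| 8 pairs, t on 7 df, trio fully shared | 5.1% | 5.0% | 5.1% |

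The unpaired test is then conservative even with the trio miscounted. The two faults pull in opposite directions.

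**6. Precision against degrees of freedom.** If matching explains a share ρ of service variance, omitting pairs inflates the SE by √[T/(T − ρ × ICC)], with T = ICC + (1 − ICC)/12.4. The 12.4 assumes 30% attrition and 17 units: 302 × 0.7/17. For ρ = 0.3 and 0.5 the ratio is 1.04 and 1.08 at ICC 3%, and 1.07 and 1.13 at ICC 6%. Against this, moving from 15 to 7 df raises the critical value by 2.365/2.131 = 1.11. A pure within-pair analysis wins in only one of these four cases, by about 2% (1.13/1.11).

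**The case against.** **The contrast of interest may be a change.** The article says changes will be compared, and it expects greater change from Time 1 to Time 2 in the intervention group. With random intercepts, stable service, pair and rural effects largely cancel from such a contrast. A calculation with 302 parents, two waves and an assumed within-person correlation of 0.5 gave the same standard error for the group-by-time term whether the top level was 19 services, 17 units, or 17 units with a set intercept (0.1135 at ICC 3%). With 30% dropout the three differed by under 0.1%. This stands as a limit on the point. It does not dispose of it: the main model lists a group indicator, the effect is reported as a mean outcome difference, and group-by-time interactions appear only for moderators.

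**Covariates are left open.** An analysis plan could add the pairs or the matching factors. That is fair for the pairing, which is the softer half. No covariate, however, turns three level-3 services into one randomised unit.

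**Stronger readings that the documents do not support.**

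- A reader might infer a larger type I error by using a normal reference. The article states no such test.
- A reader might conclude that the precision bought by matching is thrown away. Step 6 shows that lost degrees of freedom can offset much or all of the gain, so an unpaired analysis of so few pairs is defensible.
- A reader might object that no small-sample test is fixed. A condensed article commonly leaves that to the analysis plan.

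**Conclusion.** The point holds in moderate form. The top level of the stated model is not the unit that was randomised, and the matched sets have no stated place in it. Counting the trio as three clusters raises type I error to about 5.9 to 6.6% at ICC 3 to 10%. That figure assumes t on 17 df, a fully shared rural effect, no pair effect and equal service sizes, and it applies to a comparison of group means. If half of the service variance is shared within pairs, the test is conservative instead. The article gives neither correlation, so the net direction is unknown and the size is modest. For a change contrast the faults matter only if the trio or the pairs share effects on change. Nothing here makes the trial invalid. The case for correcting it is that the analysis should match the allocation and that doing so is nearly free.

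**What to change.** 1. Define the top level as the randomised unit: 16 services plus the rural trio as one, 17 in all. Reconcile Trial design, where each service is a cluster, with Randomisation, where the trio are one.
2. Reflect the matching, either by a random intercept for matched set or by adjusting for location, size and NQS rating. Say how the rural unit is used: having no real partner, it adds nothing to a within-pair contrast.
3. Base degrees of freedom on randomised units: at most 15 if unpaired, about 7 for a pure within-pair analysis.
4. Add a sensitivity analysis on the eight complete pairs.

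The cost is one recoded variable and one extra term. The downside is fewer degrees of freedom, which may offset part of the precision gained from pairing. When the article was written, Time 2 data were still being collated and no dataset had been analysed, so at that stage the choice could still be fixed before any comparison was seen.
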